
### MDMA

#### Chemistry, manufacturing, control

Pharmaceutically pure racemic MDMA HCl (±3,4-methylenedioxymethamphetamine hydrochloride) (Lipomed AG, Arlesheim, Switzerland) will be used similar to previous studies [47, 67, 68]. Quality control of the drug confirmed purity (>98%) and content of the batch and absence of decomposition products. MDMA from this lot has previously been used in human studies [67]. MDMA from the same batch is also being used in clinical trials in several countries including Switzerland [69]. MDMA will be prepared as capsules (100 mg and 25 mg) by a BAG authorized laboratory according to good manufacturing practice (GMP) criteria. Identically looking placebo capsules will contain lactose and will be provided by the same laboratory. An updated quality control certificate for the final study drug preparations and all labeling information will be provided before study initiation.

#### Metabolism and Pharmacokinetics

After a single dose of MDMA tmax is attained at 120-144 min [44, 70]. T1/2 of MDMA (100 -125 mg dose) is about 8-9 h [71]. MDMA inhibits its own metabolism possibly by forming an enzyme-metabolite complex with CYP2D6. This autoinhibition likely explains the suggested non-linear pharmacokinetics of MDMA [33, 70-72]. There are two main metabolic pathways for the metabolism of MDMA [71]. MDMA is N-demethylated to 3,4-methlyenedioxyamphetamine (MDA). MDA is an active, but minor metabolite. CYP2D6-mediated O-demethylenation followed by COMT-catalyzed methylation leads to 4-hydroxy-3-mehoxymethamphetamine (HMMA) or 4-hydroxy-3-methoxyamphetamine (HMA). HMMA is the main metabolite of MDMA [71]. HMMA and HMA are rapidly glucuronidated or sulphate-conjugated.

#### Dose selection

An oral dose of 125 mg MDMA corresponding to about 1.5-1.7 mg/kg will be used similar to previous studies [42 , 44, 46, 47, 58, 70]. This dose of pure MDMA produces moderat subjective and cardiovascular effects [24, 42, 47, 67] and is considered safe in a controlled clinical setting [2, 35, 70, 73]. The same dose of 125 mg followed 2.5 h later by 62.5 mg MDMA is currently being used in a clinical study [69]. Higher doses (150 mg or 2 mg/kg) have also been used without adverse events in MDMA studies [42, 69, 74, 75] and are used in clinical studies as well (150 mg plus 75 mg 2.5h later). Ecstasy tablets usually contain 80-160 mg of MDMA [76]. Use of more than one tablet at once is common.

### Drug-Accountability, storage and return of study drugs

The study drugs will be stored in a locked drug cabinet in a lockable room with restricted access at room temperature (15-25C) at the clinical research center. A drug dispensing and accountability log for all capsules will be kept current. The log includes the date, origin, and amount of incoming study drug. The study physician/investigator who dispenses the drug, registers and signs out the drug quantity, dispensing date of dispensing, participant number for all outgoing medications.

### Concomitant medications

Concomitant use of medications will be recorded at the screening visit and at the beginning of each study session. Subjects are asked to abstain from using drugs that may interfere with the effects of the study medications including sleeping aids, cough medications, betablocker or other substances with potentially relevant psychoactive effects. The PI may exclude subjects from study participation or reschedule sessions in the case of relevant pharmacokinetic of pharmacodynamic interactions with concomitant medications.

### Randomization and Blinding

Each subject will receive all treatments. Subjects and study personnel will be blinded to treatment order. Order is balanced and pseudo-random. A study subject number will be assigned to each subject. A treatment order is assigned to each subject number (code). Treatments are prepared and labeled according to the code by a pharmacist not involved in the study. The PI will also receive the code enclosed in an envelope. In case of a medical emergency the code can be accessed.

### Compliance

Subjects are provided with the duloxetine medication box for each session and are reminded to take the medication by a phone call the day before the study session. Compliance is assessed by asking the subject to report the time of drug intake, by collection of the empty medication box, and by determination of duloxetine in plasma (PK sample -0 and 1). During the study day medications are administered under observation by the study personnel.

# Analytics

## MDMA and metabolites

MDMA, its active metabolite MDA and the main inactive metabolites HMMA and HMA will be determined in plasma by gas chromatography-mass spectrometry (GC-MS) by established techniques as previously described [77, 44, 78].

## CYP2D6 Phenotype

Dextrorphan/dextromethorphan ratio will be used for CYP2D6 phenotyping [79, 80].

## Cortisol and prolactin

Plasma cortisol and prolactin concentrations will be determined by standard immunoassay techniques.

## Catecholamines and metanephrines

Plasma metanephrines, catecholamines, and 5-HT will be measured by HPLC with electrochemical detection at the University Hospital Lausanne.

## Copeptin

Plasma copeptin levels will be measured with a sandwich immunoassay (BRAHMS AG, Hennigsdorf, Berlin, Germany) [81].

## Duloxetine

Analysis of duloxetine plasma levels will be performed using LC-MS-MS.

# Data analysis

## Sample size estimation

Power analysis was performed with PASS®, Hintze J. Kaysville, Utah, US. We consider a relative reduction of 20% (MDMA vs. duloxetine+MDMA) in “good drug effects” to be clinically meaningful [13, 16, 17, 68]. A sample size of 13 achieves 82% power to detect a difference of 20 between the null hypothesis mean of 100 and the alternative hypothesis mean of 80 with a known standard deviation of 25 [13, 68] and with a significance level (alpha) of 0.05 using a two-sided one-sample t-test. For the most relevant secondary outcome, which is Psys, we expect that duloxetine will decrease the MDMA-induced increase in Psys by 10 mmHg from +30 mmHg (MDMA vs. placebo) to +20 mmHg MDMA+duloxetine vs. duloxetine). This effect of duloxetine would be relevant and similar to the one of citalopram on MDMA-induced increases in Psys [15]. A sample size of 8 achieves 81% power to detect a difference of 10 between the null hypothesis mean of +30 and the alternative hypothesis mean of +20 with a known standard deviation of the difference of 10 [15] and with a significance level (alpha) of 0.05 using a two-sided one-sample t-test. Assuming a drop-out rate before inclusion of 50% we will have to screen 32 subjects to include 16 in the study. Lower (8-12) [16, 17] or similar sample sizes [13, 47, 68, 82] were used in previous comparable studies. Subjects who prematurely discontinued the study for any reason will be replaced if the number of discontinued subjects exceeds three. A samples size of 8 or less is commonly used in PK studies. A larger sample is used here to produce meaningful results for the pharmacodynamic parameters.

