### Replacement policy

Subjects who withdraw from the study will be replaced if the number exceeds three subjects, to maintain at least 13 subjects. Replacement subject will follow the same treatment sequence as the withdrawn subject.

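### The stated powers of 82% and 81% are z-test figures; the t-test the protocol names gives 75% and 68%, and the floor of 13 completers rests on the first

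*Protocol*

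**What the plan says.** Protocol section 13.1 (Sample size estimation) gives two power calculations.

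- **Primary outcome**, the VAS rating of good drug effects: "A sample size of 13 achieves 82% power to detect a difference of 20 between the null hypothesis mean of 100". The mean under the alternative is set at 80, and the SD of 25 is described as known.
- **Systolic blood pressure (Psys)**, described there as the most relevant secondary outcome: eight subjects are credited with 81% power when the mean increase is +30 under the null, against "the alternative hypothesis mean of +20 with a known standard deviation of the difference of 10".

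Both calculations close by naming the same test: "significance level (alpha) of 0.05 using a two-sided one-sample t-test".

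The section then plans to include 16 subjects and to replace those who discontinue only once there are more than three. Section 14.4.7 (Replacement policy) repeats the trigger and gives its purpose: withdrawn subjects are "replaced if the number exceeds three subjects, to maintain at least 13 subjects". The floor of completers is therefore the same 13 that carries the 82% claim.

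Section 13.2 (Analysis of outcomes) plans a repeated-measures ANOVA followed by Tukey post-hoc tests.

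**The concern.** A one-sample t-test estimates the SD from the trial's own data and takes its critical value from the t distribution with n − 1 degrees of freedom. If the SD really is known, the test is a z-test with critical value 1.96. Section 13.1 claims both at once, and the choice matters at these sizes: the two-sided 5% critical value is 2.18 with 12 degrees of freedom and 2.36 with 7.

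Nothing supports treating the SDs as known. They are taken from earlier studies, and the analysis in section 13.2 estimates variance from this trial's data.

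At stake is the smallest trial the protocol accepts. Three withdrawals from 16 are allowed without replacement, on the strength of a power figure for 13. If that figure is too high, the ethics committee and the regulator have been given an overstated power for a trial size the protocol permits.

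**Working it through.** **Inputs (section 13.1).** Two-sided alpha 0.05.
- Primary: n = 13, difference 100 − 80 = 20, SD 25, standardised effect 20/25 = 0.80.
- Psys: n = 8, difference 30 − 20 = 10, SD of the difference 10, standardised effect 10/10 = 1.00.

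Both methods use λ = (difference/SD) × √n.
- Primary: λ = 0.80 × √13 = 2.884.
- Psys: λ = 1.00 × √8 = 2.828.

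**Step 1: reproduce the printed figures with a known SD (z-test).** Power = Φ(λ − 1.96) + Φ(−λ − 1.96); the second term is negligible here.
- Primary: Φ(2.884 − 1.960) = Φ(0.924) = 82.2%. Printed: 82%.
- Psys: Φ(2.828 − 1.960) = Φ(0.868) = 80.7%. Printed: 81%.

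Both match. Under this formula 13 is also the smallest n that reaches 80% for the primary outcome (n = 12 gives 79.1%), and 8 is the smallest for Psys (n = 7 gives 75.4%). This suggests the z-test calculation is where 13 and 8 came from.

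**Step 2: power of the named test.** Power = P(|T| > c), where T is noncentral t with n − 1 degrees of freedom and noncentrality λ, and c is the 97.5% point of the central t distribution.
- Primary: 12 degrees of freedom, c = 2.179, λ = 2.884, power 75.4%.
- Psys: 7 degrees of freedom, c = 2.365, λ = 2.828, power 68.1%.

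The shortfalls against the printed figures are about 7 and 13 percentage points.

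**Step 3: could another reading give both printed figures?**

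| Method | Primary, n = 13 | Psys, n = 8 |
|---|---|---|
| Printed | 82% | 81% |
| Two-sided z, known SD | 82.2% | 80.7% |
| Two-sided t (as named) | 75.4% | 68.1% |
| One-sided z | 89.2% | 88.2% |
| One-sided t | 85.8% | 81.5% |
| Two-sample z, n per arm | 53.2% | 51.6% |

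Only the two-sided z-test reproduces both. The one-sided t-test comes close for Psys by coincidence, but it misses the primary figure and the text says two-sided.

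**Step 4: t-test power over the range the protocol allows.**

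| Completers | Primary (effect 0.80) | Psys (effect 1.00) |
|---|---|---|
| 8 | – | 68.1% |
| 9 | – | 74.8% |
| 10 | 61.6% | 80.3% |
| 13 | 75.4% | 91.1% |
| 14 | 79.0% | 93.2% |
| 15 | 82.1% | 94.9% |
| 16 | 84.8% | 96.2% |

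The primary comparison first reaches 80%, and also the printed 82%, at 15 completers. Psys first reaches 80% at 10.

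**The case against.** The strongest reply concerns the consequence and leaves the arithmetic standing. It has five parts.

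1. **The planned trial has enough power by this calculation.** With all 16 subjects the t-test power is 84.8%, above the 82% claimed. The full shortfall appears only if three subjects withdraw unreplaced; one withdrawal leaves 82.1% and two leave 79.0%. This is correct. But the protocol expressly permits three, and it presents 13 as the number to be protected.

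2. **The floor itself is not settled.** Section 10.4.1 (Recruitment) says that drop-outs are replaced and gives no threshold. If that sentence governed, the floor would matter less. Sections 13.1 and 14.4.7 give the specific rule, however, and they agree with each other.

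3. **The Psys error has no operational effect.** No rule depends on 8 subjects for Psys. The interim look after 8 subjects in section 14.4.3 is a safety check unrelated to this calculation. This stands: the Psys figure is misstated, but the trial does not lack power for it.

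4. **The t-test figure is not the power of the planned analysis either.** This also stands. Suppose 25 is the SD of the within-subject difference, which section 13.1 does not say for the primary outcome. A contrast from the ANOVA with pooled error on 3(n − 1) = 36 degrees of freedom would then have 80.1% power at n = 13 unadjusted. With Tukey adjustment over the four conditions it would have about 58% at 13, 66% at 15 and 70% at 16. None of these reproduces the 82%, and the adjusted figures are lower still. How Tukey adjustment affects power is a separate question; the present point is that the printed number does not belong to the test named beside it.

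5. **The 80% mark is a convention.** The protocol never states a target power. True, but 75.4% also falls short of the protocol's own 82%, and that comparison needs no outside threshold.

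**Conclusion.** The concern holds. For the test named in section 13.1, the power is 75.4% for the primary outcome with 13 subjects and 68.1% for Psys with 8, against the stated 82% and 81%. The stated figures follow from treating the SD as known.

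The primary error carries through to the replacement rule: at the floor of 13 completers the protocol has about 7 points less power for its primary hypothesis than it claims. The Psys error stays within the text. The planned enrolment of 16 is not called into question by this calculation.

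These results assume the protocol's own effects and SDs (20 and 25; 10 and 10), two-sided alpha 0.05 and the one-sample t-test it names. They do not estimate the power of the Tukey-adjusted analysis in section 13.2.

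**What to change.** In section 13.1, delete the word known in both calculations and restate the power for the two-sided one-sample t-test:

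- **Primary:** 75% with 13 subjects, 82% with 15 and 85% with the planned 16.
- **Psys:** 68% with 8 subjects and 80% with 10.

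Then do one of two things in section 14.4.7, with the matching replacement sentence in section 13.1:

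- set the minimum at 15 completers, so that replacement starts once more than one subject withdraws (16 − 15 = 1); or
- keep 13 and state openly that a trial with 13 completers has about 75% power for the primary comparison.

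While making the edit, bring the unqualified replacement sentence in section 10.4.1 into line with the chosen rule.

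The cost is wording in these sections and less favourable stated powers. Enrolment stays at 16. Choosing 15 could mean replacing one or two subjects whom the present rule would not replace; the second option adds no subjects.

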## Analysis of outcomes

Repeated-measures analysis of variance (ANOVA) with drug (MDMA and duloxetine) as within-subject factors followed by Tukey’s post-hoc tests will be use to analyze differences between the different treatment conditions. Transformations will be performed before analysis, if response variables are nonnormally distributed. Pharmacokinetic parameters (Cmax, tmax, AUC from 0 to 6 h) will be obtained using *PK Functions for Excel*®. AUC values will be calculated by the trapezoidal rule. Additional PK analyses may be performed using *WinNonLin®* and *GraphPad®.* Statistical analyses will be performed using *Statistica*® *(StatSoft).*

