## Potential risks

Physical risks:

MDMA: A large series of phase I like studies have been performed using MDMA [13-16, 24, 42, 44-47, 57, 58, 67, 68, 70, 71, 74, 75, 82-91]. This considerable body of evidence indicates that the likelihood for significant toxicity from doses of MDMA such as the one to be used in the present study and in controlled settings is very low. Thus, no lasting biological or psychological injury is expected. See below for specific MDMA toxicity and monitoring. Expected adverse effects of MDMA:MDMA is expected to produce moderate acute adverse effects such as increased jaw muscle tension, dry mouth, dizziness, palpitations, tremor, nausea, headache, insomnia, and transient anxiety in more than 10% of subjects, [15, 42]. MDMA is expected to produce sequelae (1-3 days post MDMA) including difficulty concentrating, irritability, or slightly depressed mood in more than 10% of subjects [15]. No severe or serious adverse effects are expected. Duloxetine: In placebo-controlled double-blind trials in patients duloxetine (60-120 mg/day) produced nausea (20-29%), headache (20%), dry mouth (15-18%), insomnia (11-15%), fatigue (14%), dizziness (9-11%), constipation (11%), decreased appetite (8%), and sweating (6%) [63]. Adverse effects of duloxetine in healthy volunteers similary include nausea, dry mouth, insomnia, dizziness, sweating, and clinically non-significant increases in blood pressure or heart rate [25, 61, 92]. No severe or serious adverse effects are expected.

Venipunction: There is a risk for pain, bruising and thrombophlebitis.

Risk to privacy of subjects: Potential risks of data collection include breach of confidentiality. Financial risks: There is no risk of expense to the subject. Insurance coverage is provided. Travel expenses are expected to be minimal and are included in the compensation of 1000 CHF per subject.

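### The Psys hypothesis is a difference of differences, but section 13.2 points to Tukey pairs without naming the interaction as the deciding test, and the 81% power at n = 8 is not that of the t-test named

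*Protocol*

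**What the plan says.** Protocol section 13.1 introduces the calculation with "For the most relevant secondary outcome, which is Psys" and expects duloxetine to "decrease the MDMA-induced increase in Psys by 10 mmHg from +30 mmHg (MDMA vs. placebo) to +20 mmHg MDMA+duloxetine vs. duloxetine". Section 9.2 words the hypothesis the same way: what is to be reduced is the rise that MDMA produces. The sizing is then written as a one-sample problem, to "detect a difference of 10 between the null hypothesis mean of +30 and the alternative hypothesis mean of +20". The spread enters this calculation as a fixed quantity: "with a known standard deviation of the difference of 10". The error rate and the test are given next: "with a significance level (alpha) of 0.05 using a two-sided one-sample t-test". The result is "A sample size of 8 achieves 81% power". Section 13.1 does not say which difference the SD of 10 describes.

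Section 13.2 plans a repeated-measures ANOVA with MDMA and duloxetine as within-subject factors, after which Tukey's "post-hoc tests will be use to analyze differences between the different treatment conditions". It does not single out any term of the ANOVA, or any pair, as the test of the Psys hypothesis.

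Section 14.1 includes "clinically non-significant increases in blood pressure or heart rate" among the adverse effects of duloxetine in healthy volunteers, without a size or a frequency.

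Enrolment is 16 (section 13.1), and withdrawals are replaced so that at least 13 remain (section 14.4.7).

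**The concern.** Section 13.1 defines the Psys effect by four conditions: MDMA against placebo, compared with duloxetine-MDMA against duloxetine. A Tukey comparison uses two conditions. Of the six possible pairs, none is the contrast in 13.1. The closest, MDMA versus duloxetine-MDMA, differs from it by whatever duloxetine does to Psys on its own, and section 14.1 gives some reason not to assume that this is zero. A rise too small to matter clinically can still matter against a 10 mmHg target.

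The ANOVA offers several F-tests and Tukey offers six pairs. Without a rule on which of them decides attenuation, the choice for the leading secondary outcome could be made after the data are seen. The power statement does not settle the matter, because it is labelled as one test, computed as another, and silent on whose SD it uses.

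**Working it through.** **Inputs.** Effect 10 mmHg (+30 against +20), SD 10, two-sided alpha 0.05, n = 8, stated power 81% (section 13.1). Sample size 16, floor 13 (sections 13.1 and 14.4.7). Four within-subject conditions (section 10.1). The effect of duloxetine alone on Psys, the correlation between the two differences, and sphericity are not in the protocol and are assumed below.

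**1. The plan's own figure.** With the SD treated as known, power = Φ(δ√n/SD − 1.96) = Φ(10 × √8/10 − 1.96) = Φ(2.828 − 1.96) = 80.7%. This reproduces the stated 81%. The one-sample t-test that 13.1 names (noncentral t, 7 df, noncentrality 2.828) gives 68.1%, and needs n = 10 for 80%. The primary outcome shows the same pattern: n = 13, difference 20, SD 25 gives 82.2% by the normal formula (stated 82%) and 75.4% by the t-test.

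**2. Hypothesis against pair.** Let P, D, M and DM be mean Psys under placebo-placebo, duloxetine-placebo, placebo-MDMA and duloxetine-MDMA, and let x = D − P.

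- Hypothesis: (M − P) − (DM − D) = 30 − 20 = 10.
- Pair: M − DM = [(M − P) − (DM − D)] − (D − P) = 10 − x.

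The two agree only at x = 0. The interaction does not depend on x.

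**3. Tukey power for that pair.** True double difference held at 10; paired-difference SD 10 and sphericity assumed; noncentrality (10 − x)√n/10. The Tukey critical value on the t scale for four conditions is 2.693 at n = 13 (36 df) and 2.668 at n = 16 (45 df).

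| x (assumed, mmHg) | M − DM | Noncentrality, n = 16 | Power, n = 13 | Power, n = 16 |
|---|---|---|---|---|
| 0 | 10 | 4.0 | 81% | 90% |
| 2.5 | 7.5 | 3.0 | 51% | 63% |
| 5 | 5 | 2.0 | 20% | 27% |

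Under the same assumptions the error variance is 10²/2 = 50, so the double difference has variance 4 × 50 = 200 and SD 14.1. Interaction power is then 65% (n = 13) or 75% (n = 16) at every x. The pair is therefore the more powerful test at x = 0 and the less powerful one by x = 2.5.

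**4. Interaction power and the meaning of SD 10.** If 10 is the SD of the double difference, testing +20 against a fixed +30 is the same as testing −10 against 0, and no sampling error is lost. If 10 is the SD of one drug-versus-control difference, and the two differences have equal SDs and correlation ρ, the double difference has SD 10√(2(1 − ρ)). One-sample t-test power for a true value of 10:

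| ρ (assumed) | SD of double difference | n = 13 | n = 16 |
|---|---|---|---|
| −0.25 | 15.8 | 55% | 66% |
| 0 | 14.1 | 65% | 75% |
| 0.25 | 12.2 | 77% | 86% |
| 0.5 (same as SD 10 for the double difference) | 10.0 | 91% | 96% |

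For 80% power the t-test needs 10 subjects at SD 10 and 18 at SD 14.1.

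**The case against.** The best defence is that the right test is already in the plan. A two-factor within-subject ANOVA on these four conditions has an MDMA × duloxetine interaction, and its F-test on 1 and n − 1 df is the one-sample t-test on each subject's difference of differences. A main effect of duloxetine does not bias it. This stands: the plan lacks no suitable test. It leaves open which test decides, and its wording leads to the pairs. Saying that such detail belongs in an analysis plan is a partial answer only, because the protocol itself fixes a hypothesis, a sizing and a post-hoc procedure that do not match.

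Second, the plainest reading of 13.1 attaches the SD of 10 to the 10 mmHg difference just named. On that reading the fixed +30 does no harm. Individual responsiveness to MDMA would also tend to correlate the two differences positively and pull the SD below 14.1. Both points are fair; the text does not settle which SD is meant.

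Third, section 14.1 lists a possible rise in blood pressure or heart rate, with no size. A reader might infer that duloxetine's own pressor effect will hide a real attenuation. The protocol does not support this: 2.5 and 5 mmHg are illustrations, and the interaction test is unaffected by them.

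Last, MDMA versus duloxetine-MDMA is a legitimate question, and the Tukey pairs need not be dropped.

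**Conclusion.** The point holds as a mismatch to be repaired in the text for a secondary outcome. The hypothesis in 13.1 is the interaction; 13.2 contains that term but does not name it as deciding and directs the reader to pairs that answer the same question only if duloxetine alone leaves Psys unchanged. How much this matters depends on an effect that the protocol does not quantify. At n = 16, under the stated assumptions, the Tukey pair has 90% power if that effect is zero, 63% at +2.5 mmHg and 27% at +5 mmHg.

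Separately, and without any such assumption, the 81% at n = 8 is wrong for the test it names: the t-test gives 68%. That gap comes wholly from treating the SD as known, and owes nothing to the double difference or to Tukey.

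A reader might also infer that the trial is too small for Psys. The protocol does not show this. The n = 8 figure does not set enrolment, and power at n = 13 to 16 is 91% to 96% if SD 10 belongs to the double difference. It is 65% to 75% only if SD 10 belongs to a single drug-versus-control difference and the two differences are uncorrelated.

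**What to change.** - **Section 13.2:** name the MDMA × duloxetine interaction contrast, (MDMA − placebo) − (duloxetine-MDMA − duloxetine), as the test of attenuation of blood pressure and heart rate. Report it in mmHg or beats/min with a 95% confidence interval. Keep the Tukey pairs as supportive.
- **Section 13.1:** say which difference has the SD of 10. Replace the 81% at n = 8 with t-based power for the interaction contrast at n = 13 to 16: 91% to 96% if the SD is that of the double difference. If it is that of a single difference, state the assumed correlation (65% to 75% when it is zero).
- **Enrolment:** leave at 16 with the floor of 13.

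The cost is a few sentences. The planned ANOVA already yields the contrast, so no new data, visits or subjects are needed.
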